### Accessibility, usability and acceptability assessments

Given the novelty of the digital therapy platform, its accessibility, usability and acceptability will be assessed in the SlowMo arm. This will be done through assessment of current mobile use and confidence at the beginning of therapy, monitoring of connectivity for the web app, system analytics data on the use of the platform, the User Experience Survey (adapted from [35]), and a service-user led qualitative interview with a sub-sample of those receiving SlowMo (*n* = 20).

### Therapy adherence assessments

In the SlowMo arm, therapy adherence will be assessed from the number and duration of sessions attended, and system analytics data on mobile app use. Therapy delivery will be evaluated in terms of fidelity to the treatment manual.

### Data management and security

All data will be anonymised at source. All personal data will be kept in a locked filing cabinet in a locked office and will be kept separate from all the research data. Therapy files will be kept in a secure office in the clinic and will not be accessible to the staff collecting the research outcome data. Data will be entered on a computerised database, held centrally and managed by King’s College London CTU, by research assistants using a secure network connection. Audio-recording equipment will be used to record assessments to check fidelity to assessment protocols and to ensure interrater reliability. The therapy sessions will be audio-recorded (with participant consent) for monitoring the intervention in terms of fidelity and competence. These audio files, named with a unique participant identifier, will be stored as computer files on secure NHS/university servers.

Security and privacy of information stored on the app has been considered throughout its development. If informed consent is provided, app data will only be synched during therapy sessions, over secure connections and stored on a password-protected, secure database. Data transferred will only contain a name (chosen by the person) and a Unique Device Identifier (UDID) which is generated automatically by the therapy platform, and will match the anonymised participant number. Participants can also opt to use the app in a fully offline mode. Participants will have the opportunity, if they wish, to password protect the handset with a pin number or password. During the informed consent process potential participants will be made fully aware of the data collected by the platform, and how data will be stored and used. Access to this privacy and security information is also available from the settings menu of the app, which consenting participants can access at any time.

### Data quality

Data quality will be ensured by close monitoring and routine auditing for accuracy throughout the data collection period. In order to ensure the accuracy of the data entered into the database, the main outcome measure entry will be checked for every participant by comparing the paper record with that on the database. An error rate of no more than 5% is acceptable. This will be done once all possible assessments for each time point have been completed. If the error rate is higher than 5%, advice will be sought from the trial statistician and methodologist regarding further data checking.

### Sample size

Recruitment of 360 participants will be split equally across sites. We have powered the study conservatively to detect a clinically meaningful 10-point reduction in the primary outcome measure (GTPS [36]); based on a standard deviation of 25, this is a 0.4 effect size [10]. We account for: clustering in the SlowMo arm with an intraclass correlation coefficient (ICC) = 0.01 with 10 therapists (no clustering in the TAU arm), 1:1 allocation, 0.05 significance level. Calculations used Clsampsi in Stata. A simple two-tailed *t* test with 150 people per group gives 90% power to detect an effect size of 0.4, and 80% for 0.35. In practice, power will be increased by using multiple regression. To allow for conservatively high 20% attrition we will recruit 360 patients at baseline split equally across three sites (120 per site, 60 per arm per site). For the mediational analyses, a sample of *N* = 300 has > 80% power to detect a proportion mediated of 40%, and > 70% power to detect a proportion mediated of 30%, corresponding to findings in our pilot work [12] (calculated using PowerMediation in R).

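### The 20% attrition allowance was applied as 300 × 1.2 rather than 300 / 0.8, so 360 recruited leave 288 evaluable, not the 300 behind the power figures (minor)

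*Protocol article*

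**What the plan says.** All the relevant figures are in the Sample size section of the protocol article.

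- **Primary power:** a two-tailed t test "with 150 people per group gives 90% power to detect an effect size of 0.4, and 80% for 0.35". The target difference is 10 points; "based on a standard deviation of 25, this is a 0.4 effect size".
- **Design inputs:** "1:1 allocation, 0.05 significance level", and an "intraclass correlation coefficient (ICC) = 0.01 with 10 therapists (no clustering in the TAU arm").
- **Recruitment:** "To allow for conservatively high 20% attrition we will recruit 360 patients at baseline split equally across three sites", that is 120 per site and 60 per arm per site.
- **Mediation:** for N = 300 the section claims more than 80% "power to detect a proportion mediated of 40" per cent, and more than 70% power for a proportion of 30%.

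The section adds that multiple regression will raise power in practice, without giving an amount. The Statistical analysis section plans random effects models on the repeated measures, adjusted for baseline, with missing outcomes handled under Missing At Random.

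**The concern.** Both power statements are tied to 300 participants with outcome data. The recruitment target is presented as the number that protects those 300 against a 20% loss, and it does not. The target equals the evaluable number increased by 20%, whereas attrition is a fraction of those recruited, so the evaluable number should be divided by the retention rate.

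What is at stake is the accuracy of a stated design property: how much attrition the trial can absorb before it drops below its planned evaluable sample. The mediation claim is affected as well. It concerns one of the three primary hypotheses and has no attrition allowance other than the 360.

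**Working it through.** **Inputs from the Sample size section:** 150 per group, effect sizes 0.40 and 0.35, two-sided alpha 0.05, 1:1 allocation, ICC 0.01, 10 therapists in the SlowMo arm only, 20% attrition, 360 recruited.

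**Step 1. Attrition**

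- Needed for 300 evaluable at 20% loss: 300 / (1 − 0.20) = 375 (188 per arm if each arm is rounded up).
- Stated target: 360 = 300 × 1.20.
- Evaluable from 360 at 20% loss: 360 × 0.80 = 288, or 144 per arm.
- Shortfall: 15 recruited, or 12 evaluable (12 / 300 = 4%).
- Attrition at which 360 still yields 300: 1 − 300/360 = 16.7%.

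**Step 2. Reproducing the stated power at 150 per arm**

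The SlowMo arm has 150 / 10 = 15 participants per therapist, so its design effect is 1 + (15 − 1) × 0.01 = 1.14. In SD units the standard error is √(1.14/150 + 1/150) = 0.1194. The noncentrality is 0.40 / 0.1194 = 3.35, or 0.35 / 0.1194 = 2.93.

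The Satterthwaite degrees of freedom are (v1 + v2)² / (v1²/9 + v2²/149), with v1 = 1.14/150 and v2 = 1/150. This gives about 30.

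**Step 3. The same at 144 per arm**

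The design effect is 1 + (14.4 − 1) × 0.01 = 1.134, and the standard error is √(1.134/144 + 1/144) = 0.1217.

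| Method | 150 per arm: d = 0.40 / 0.35 | 144 per arm: d = 0.40 / 0.35 |
|---|---|---|
| Stated in the protocol | 90% / 80% | not given |
| Clustered t, Satterthwaite df ≈ 30 | 90.0% / 81.0% | 88.9% / 79.5% |
| Clustered, normal approximation | 91.8% / 83.4% | 90.8% / 82.0% |
| Unclustered t test | 93.2% / 85.6% | 92.3% / 84.1% |

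The first calculated row comes closest to the protocol's figures. The document names the Stata routine (Clsampsi) but no degrees-of-freedom method, so that row is an inference. Within every row the drop from 150 to 144 per arm is about 1 point at d = 0.40 and about 1.5 points at d = 0.35.

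**Step 4. Covariate adjustment**

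The document gives no baseline–outcome correlation. Assuming r between 0.2 and 0.5, and multiplying the variance in the clustered normal approximation by 1 − r², power at 144 per arm is 91.8% to 96.7% for d = 0.40 and 83.5% to 91.3% for d = 0.35.

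**Step 5. Mediation**

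No path values are given, so the stated power cannot be reproduced. As a worst case, suppose power at N = 300 were exactly 80% and 70%, with noncentrality proportional to √N. At 288 the noncentrality shrinks by √(288/300) = 0.980, and power becomes 78.4% and 68.2%. Because the protocol states only lower bounds, the true values may be higher.

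**The case against.** The strongest reply is that the slip changes almost nothing, and most of that reply stands. A reader might infer that the trial fails to deliver its 90% and 80% power. The documents do not support this. Two of the three methods in the table still exceed both figures at 144 per arm. The third falls short by 1.1 and 0.5 points and depends on an assumed degrees-of-freedom method. At whole-percent precision its 79.5% is hard to tell from 80%. The stated power also excludes the gain from regression. In addition, the repeated-measures model uses partial data: someone assessed at 12 weeks but not at 24 still contributes, so 288 is not strictly the analysed number.

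A reader might also infer that the mediation power is breached. That cannot be shown, because the protocol gives only lower bounds and no inputs.

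A third tempting reading is that attrition between 16.7% and 20% would be passed as within plan. The Research governance section has the Trial Steering Committee audit recruitment and data completion, but it sets no attrition threshold, so this is speculation.

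It could finally be said that 20% was meant relative to the 300 rather than to those recruited. The sentence offers 360 at baseline as the allowance for attrition, and loss from a baseline sample is ordinarily counted against that sample. If another meaning was intended, the text should say so.

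None of this reconciles 150 per group, 20% and 360 with one another.

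**Conclusion.** The statement is wrong as written, and the error is minor. That 360 recruited give 288 evaluable at 20% attrition is plain arithmetic and needs no assumption beyond counting attrition against those recruited. The same holds for the 375 needed to keep 300, and for the 16.7% that 360 can absorb.

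The cost in primary power is about 1 to 1.5 points. Whether 90% and 80% are narrowly missed or still met depends on a calculation method that the document does not fully specify. For mediation, only the shortfall from 300 to 288 is established.

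**What to change.** Keep 360 and make the text consistent in one of two ways.

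1. State that 360 allows for about 16.7% attrition, leaving 300 evaluable. The power figures can then stand as printed.
2. Keep 20% and state that 288 are evaluable (144 per arm). Re-run the primary power at 144 per arm in the original Clsampsi set-up and report the result with its degrees-of-freedom method. Expect about 89% and 79.5% if a Satterthwaite t was used. Re-run the mediation power at N = 288 and give its path inputs.

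Either way the cost is wording, plus two short recalculations under the second option. No further participants are needed. The price is a smaller stated attrition allowance in the first case, and slightly less favourable stated power in the second.

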### Statistical analysis

We will report all participant flow, and analyses will be conducted on the ITT population: all participants will be randomised regardless of non-compliance with protocol or withdrawal from the study. Analyses will post-date final follow-up assessments, with due consideration of potential biases from loss to follow-up. The primary analysis will test for a treatment effect on the primary and secondary clinical outcomes. Random effects regression models allowing for clustering by both participants and therapists will be fitted to the repeated measures, controlling for treatment site, baseline paranoia severity and the corresponding baseline assessment for the outcome under investigation. We will allow for missing outcome data under the Missing At Random assumption [60]; we may also use inverse probability weighting to adjust for non-adherence to allocated treatment and other intermediate outcomes as predictors of future loss to follow-up [61]. Secondary analyses will test treatment-effect mechanisms, moderation and process/adherence effects using modern causal inference methods [62, 63]. The trial outcomes will comprise two parallel series of longitudinal data: one for the putative mediators (M) and one for the clinical outcomes (Y).

For the mechanistic analysis, to test for a treatment effect on the putative mediator, we will replace the clinical outcome with the mechanistic variable as the dependent variable in the random-effect models. If we separately demonstrate a treatment effect on both the putative mediator and on the clinical outcome, we will evaluate mediation in these parallel longitudinal data sets through the use of parallel growth curve and latent change models [64, 65]. These models preserve the basic mediation model by replacing observed variables with latent constructs – the growth factors driving the temporal responses, M_1_ to M_p_ and Y_1_ to Y_p_. Importantly, the mediational structure only applies to the slope growth or change factors since randomised treatments are independent of the intercept growth factors (baseline values). Growth curve and latent change models can be estimated by maximum likelihood and other methods using the software package Mplus [66]. The application of these methods to mechanism evaluation within EME (Efficacy and Mechanism Evaluation) trials is illustrated in [62]

The aim of these analyses is to demonstrate that the effect of treatment on the growth (change) in the clinical outcome (Y) is explained (caused) by its effect on the growth (change) in the mediator. The major challenge to a valid inference is that there may be confounding of the mediator and outcome. We will begin by allowing for baseline values of the mediator and of the clinical outcome, as in the analyses of the successful EME Worry Intervention Trial [10]. We will then check the sensitivity of the results to the possibility of hidden confounding (unmeasured variables) through the use of instrumental variable methods [62, 63].

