### Aims

We aim to test the clinical efficacy of SlowMo over 24 weeks compared to TAU to determine the mechanisms through which it reduces paranoia, and to identify participant characteristics that moderate its effectiveness (either by moderating the degree of change in the mechanism, or by influencing adherence to the intervention). We will test the hypothesis that changes in fast thinking mediate changes in our primary outcome of paranoia severity. Consistent with our interventionist causal approach, we do not hypothesise that worry is a mediator, as it is not targeted in the SlowMo intervention, even though changes in worry did mediate changes in paranoia in a recent trial, when it was the treatment target [10]. However, we will examine any observed effects. In addition, we have preliminary evidence of modifiers of treatment effects that we will also take the opportunity to investigate. Using a randomised controlled trial design, we have selected TAU as the comparator condition. This is because there is a very low penetration of evidence-based psychological treatment in the NHS, and thus the key efficacy question to address at this stage is whether SlowMo confers benefits over and above standard care. An important secondary goal is to evaluate mechanisms of action; the trial hypotheses concern reasoning, and are best tested where the control condition is inactive with respect to the targeted psychological processes.

The main research questions are as follows:Is SlowMo efficacious in reducing paranoia severity over 24 weeks, when added to TAU, in comparison to TAU alone?Does SlowMo reduce paranoia severity by improving fast thinking (reducing belief inflexibility and jumping to conclusions)?Do participant characteristics (i.e. their cognitive capacities, specifically working memory and thinking habits; and their symptoms, specifically negative symptoms) moderate the effects of the intervention?Does outcome differ by adherence to the intervention and is adherence predicted by the participants’ beliefs about their illness and about the intervention?Does the SlowMo digital therapy platform have acceptable rates of usability, acceptability and adherence?Does SlowMo lead to changes in the following secondary outcomes: other delusional symptoms, wellbeing, quality of life, self and others schemas, service use and worry

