### Hypotheses

Primary hypotheses:The intervention will reduce paranoia severity over 24 weeksFast thinking (belief inflexibility and jumping to conclusions) will improve in response to the interventionReductions in fast thinking will mediate positive change in paranoia severity

Secondary hypotheses:4.Poorer working memory and more severe negative symptoms will negatively moderate treatment effects5.Therapy adherence will moderate the effects of treatment on outcome and adherence will be predicted by beliefs about mental health problems6.Worry will not mediate reductions in paranoia severity

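### Mediation is evaluated only after a demonstrated effect on paranoia itself, so a hypothesis listed as primary can go unexamined; the power cost is modest at the planned effect and large below it

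*Protocol article*

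**What the plan says.** All references are to the protocol article.

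- **Hypotheses.** Mediation of the change in paranoia by fast thinking is the third of three hypotheses headed primary. A secondary hypothesis is also about mediation: "Worry will not mediate reductions in paranoia severity".
- **Aims.** The test is promised with no condition: "We will test the hypothesis that changes in fast thinking mediate changes in our primary outcome of paranoia severity". The same section then says: "An important secondary goal is to evaluate mechanisms of action".
- **Sample size.** Mediation has its own power statement. With N = 300 the article claims more than 80% "power to detect a proportion mediated of 40" per cent, and more than 70% for 30 per cent. No condition is mentioned.
- **Statistical analysis.** Mechanisms are placed among the secondary analyses: "Secondary analyses will test treatment-effect mechanisms, moderation and process/adherence effects using modern causal inference methods". The rule at issue follows: "If we separately demonstrate a treatment effect on both the putative mediator and on the clinical outcome, we will evaluate mediation".

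The article does not say what is reported if the condition fails. The instrumental-variable step is a sensitivity check on the same conditional analysis, not a separate route to the hypothesis.

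**The concern.** The rule has two halves: an effect must be shown on the mediator and on the clinical outcome. The mediator half is harmless for power, because an indirect effect cannot be shown without that path. The outcome half is different. The test of the total effect on the GPTS carries the full variance of the outcome, and a null or opposing direct path can dilute it. It can fail while the indirect effect is well estimated.

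If the GPTS comparison narrowly missed significance, the trial would leave a hypothesis it calls primary unexamined with the data already collected. The Aims and Hypotheses lead a reader to expect an answer that the Statistical analysis section withholds in that case. Selecting on significance may also distort the mediation estimates that do get reported.

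**Working it through.** **1. The article's own figure for the outcome half.** Inputs from Sample size: "1:1 allocation, 0.05 significance level", and "A simple two-tailed *t* test with 150 people per group gives 90% power to detect an effect size of 0.4, and 80% for 0.35". Approximate power is Φ(d·√(n/2) − 1.96), with n per arm.

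- No clustering, n = 150: at d = 0.4, Φ(0.4 × 8.660 − 1.96) = Φ(1.504) = 93.4%. At d = 0.35, 85.8%.
- Ten therapists give 15 participants each, so the design effect is 1 + 14 × 0.01 = 1.14. Applied to the SlowMo arm only: 91.8% and 83.4%. Applied to both arms: 90.1% and 81.0%.

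The stated 90% and 80% therefore reproduce once clustering is allowed for, and are slightly conservative.

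**2. Set-up for mediation.** The mediation power cannot be reproduced exactly because neither path is given. Assumptions:

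- One mediator, one time point, no clustering, no baseline adjustment, no mediator–outcome confounding.
- Within-arm SD of 1 for mediator and outcome. One unit is 25 GPTS points.
- N = 360 × 0.8 = 288, the number left after the article's 20% attrition.
- Treatment effect on the mediator a = 0.4 SD; 40% of the total effect mediated, so a·b = 0.4d and b = 0.4d / a.
- Demonstrated is read as two-sided p < 0.05. The indirect effect is tested by the Sobel statistic.

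**3. Which half of the rule costs power.** The Sobel statistic satisfies 1/z² = 1/z_a² + 1/z_b², so |z| is always below |z_a|. A significant indirect effect already implies a significant effect on the mediator. The loss comes from the outcome half alone.

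**4. Results.** The total-effect column uses the formula in step 1 with n = 144; the last three columns come from simulation.

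| Total effect d | GPTS points | a·b | b | Power, total effect | Mediation significant, no condition | With condition | Loss (points) |
|---|---|---|---|---|---|---|---|
| 0.40 | 10 | 0.16 | 0.40 | 92% | 91% | 85% | 6 |
| 0.35 | 8.75 | 0.14 | 0.35 | 84% | 91% | 79% | 12 |
| 0.25 | 6.25 | 0.10 | 0.25 | 56% | 86% | 50% | 36 |

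Repeat runs differ by about one percentage point. As a rough check, the product of the two separate powers is 0.91 × 0.92 = 0.84, 0.91 × 0.84 = 0.76 and 0.86 × 0.56 = 0.48. The simulated joint figures are slightly higher because the two tests are positively correlated.

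For 30% mediated at d = 0.4 and a = 0.4, the figures are 90% without and 84% with the condition, against a stated figure above 70%.

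**5. Effect of selection on the estimates (N = 288, 40% truly mediated).**

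| d | a | Median proportion mediated, all trials | Trials meeting the condition |
|---|---|---|---|
| 0.4 | 0.3 | 0.40 | 0.43 |
| 0.4 | 0.4 | 0.40 | 0.40 |
| 0.4 | 0.5 | 0.40 | 0.39 |
| 0.2 | 0.4 | 0.37 | 0.27 |

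At d = 0.4 and a = 0.4 the mean indirect effect among selected trials is 0.169 against a true 0.160, a difference of 0.009 × 25 = 0.2 GPTS points. At a = 0.3 it is 0.191 against 0.160, or 0.8 points. The distortion has no fixed direction and is negligible in the planning case.

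**The case against.** The rule can be defended. Hypothesis 3 is worded as explaining a change in paranoia, which presupposes a change to explain, and looking at mechanisms after efficacy is a recognised, conservative order. The article twice calls mechanism evaluation secondary. At the planned effect the cost is about six points, and the larger losses need a total effect below the 10 points the article calls clinically meaningful. The advantage of an unconditional test also assumes an unconfounded path from mediator to outcome, whereas the article names confounding there as the major challenge. An apparent indirect effect beside a null total effect is what such confounding could produce. The effect on fast thinking (hypothesis 2) is tested in any case.

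These points stand as limits on severity. They do not remove the conflict: the secondary label contradicts the Hypotheses section, and the Aims attach no condition.

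A reader might go further in three ways that the document does not support.

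- *That the rule pushes mediation power below the stated figure.* At the planned effect the conditional 85% is still above 80%. The 79% at d = 0.35 does not refute the claim, since the article does not say which total effect underlies it. A weak path (a = 0.3) does not either: the mediator test alone then has only about 72% power at N = 288 and about 73% at N = 300, so it cannot be the basis of a claim above 80%.
- *That any reported proportion mediated is biased because its denominator is selected to be large.* The article uses that scale for power and does not promise to report the quantity. The shift can go either way and is absent in the planning case.
- *That losses of 40 points or more are to be expected.* Falls such as 99% to 57% need the effect to be wholly mediated with a total of 0.25 SD, far from the planned 30–40% mediated and 0.4 SD.

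**Conclusion.** The concern holds in limited form. The article lists mediation as a primary hypothesis and promises its test unconditionally, but then makes it depend on a demonstrated effect on the GPTS, which estimating an indirect effect does not require. The cost is about 6 percentage points at the planned effect, 12 at the article's own 0.35 SD case and 36 at 0.25 SD. These sizes rest on assumed paths, a simple unconfounded single-mediator model and the reading of demonstrated as p < 0.05, which the article does not define. Distortion from selection is a minor addition, relevant mainly if the effect is smaller than planned or the path to the mediator is weak.

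This should be fixed but is not critical: the primary efficacy comparison, its error rate and the sample size are untouched.

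**What to change.** Drop the total-effect condition. For each pre-specified mediator, and for worry, estimate the indirect effect in GPTS points with a 95% confidence interval whatever the total-effect test shows. Keep the planned sensitivity analyses for confounding. Give a proportion mediated only descriptively, and only when the total effect is clearly away from zero. Covering worry matters because the article does not say whether the rule extends to it; if it does, mediation by worry (hypothesis 6) could also go unevaluated.

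The cost is one sentence and a little more analysis. The drawback is that an indirect effect beside a null total effect must be worded cautiously, since mediator–outcome confounding could explain it.

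If the condition is kept, describe hypothesis 3 as conditional in the Aims, Hypotheses and Statistical analysis sections alike, and restate the mediation power with the condition included and the assumed paths given.

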### Assessments and follow-up

#### Assessment of efficacy

Participants will complete a range of self-report and interview-based measures to assess the impact of the interventions on primary and secondary outcomes, the hypothesised mediators, and other key processes implicated in paranoia and response to therapy. Assessments will be completed at baseline, 12 and 24 weeks. Every effort will be made to ensure that data collection and completeness is optimised throughout the trial, and to minimise attrition/loss to follow-up. Please refer to Fig. 3 (SPIRIT Figure) for details of assessment at each visit. Assessments will be audio-taped (after first establishing consent) to allow evaluation of adherence to the research protocol and assessment ratings.

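### For hypothesis 3, the stated mediation model names only baseline mediator and baseline outcome as covariates and states no lag; measured common causes and reverse causation are left without a stated place

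*Protocol article*

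**What the plan says.** All of this is in the protocol article. Under Hypotheses, the third primary hypothesis is that reduced fast thinking mediates the improvement in paranoia. Under Statistical analysis, mechanism is a secondary analysis. It is attempted only if treatment is shown to affect both mediator and outcome, and is carried out "through the use of parallel growth curve and latent change models". In these, "the mediational structure only applies to the slope growth or change factors". The aim is causal: to show that the treatment effect on outcome change "is explained (caused) by its effect on the growth (change) in the mediator".

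The same section recognises the threat: "The major challenge to a valid inference is that there may be confounding of the mediator and outcome". The response has two steps. The first is "We will begin by allowing for baseline values of the mediator and of the clinical outcome". The second is "We will then check the sensitivity of the results to the possibility of hidden confounding (unmeasured variables) through the use of instrumental variable methods". The instruments are not named.

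Other parts of the article bear on the point. Under Assessment of efficacy, "Assessments will be completed at baseline, 12 and 24 weeks". Therapy lies within 12 weeks (Planned trial interventions). GPTS is rated over the preceding month. Under Hypotheses, "Poorer working memory and more severe negative symptoms will negatively moderate treatment effects". Worry and schemas are also collected. The treatment-effect models adjust for site, baseline paranoia severity and the baseline of the outcome.

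**The concern.** Randomisation protects the paths from treatment to mediator and from treatment to outcome. It does not protect the path from mediator to outcome. Any baseline factor that drives both reasoning change and paranoia change will make that path look non-zero.

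The two stated steps deal with baseline mediator and outcome, and with what was not measured. Factors that are measured fall between them. Working memory and negative symptoms are plausible common causes, because the Background reports that people with more of these difficulties benefitted less. Worry is plausible too, because the Aims section says that change in worry mediated change in paranoia in an earlier trial.

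The second gap is direction. If change in fast thinking and change in paranoia are related over the same period, a fall in paranoia that loosens conviction looks the same as the hypothesised effect. The one-month GPTS recall adds to this, since a 12-week GPTS covers roughly weeks 8 to 12 and so largely precedes the mediator rated at that visit.

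At stake is the conclusion on mechanism, not the conclusion on efficacy.

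**Working it through.** **The plan's own figure.** The Sample size section gives N = 300 more than 80% power for 40% mediated and more than 70% for 30%. It does not give the treatment-to-mediator effect *a*, so *a* is varied here. With total effect 0.4 SD and proportion mediated *P*, b = 0.4P/a, SE(a) = √(1/(300 × 0.25)) = 0.1155, SE(b) = √((1 − b²)/300), and the Sobel z = ab/√(a²SE(b)² + b²SE(a)²). At a = 0.4 and P = 0.4: b = 0.4, SE(b) = 0.0529, z = 0.16/0.0508 = 3.15, power 88%. Over a = 0.4 to 0.8, power is 88–94% for P = 40%. For P = 30% it is 83%, 86%, 83%, 77% and 69% at a = 0.4, 0.5, 0.6, 0.7 and 0.8. The stated figures are attainable but cannot be checked exactly.

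**Simple algebra, assumed strengths.** Take unit within-arm variances, total effect 0.4, a = 0.4 and a true mediator-to-outcome effect of zero.
- Omitted factor with effect *r* on both mediator and outcome, beyond their baselines: apparent b = r², indirect effect 0.4r², proportion 0.4r²/0.4 = r². This is 9%, 16% and 25% at r = 0.3, 0.4 and 0.5.
- Pure reverse causation, outcome-to-mediator slope 0.5: a = 0.5 × 0.4 = 0.2, apparent b = 0.5, indirect effect 0.10, proportion 0.10/0.40 = 25%.

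**Simulation.** N = 300, visits at 0, 12 and 24 weeks, true mediation zero, treatment effect 0.4 on both series, 1,500 replicates. Change-on-change regression adjusted for baseline mediator and outcome stands in for the latent model. C is a baseline covariate affecting both series at each follow-up visit. Entries are two-sided 5% rejection rates for the mediator-to-outcome path, and the spurious proportion mediated under the stand-in.

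| Assumed truth | Stand-in | Spurious proportion | Stand-in + C | 12-week M to 24-week Y, adjusted for 12-week Y | Same + C |
|---|---|---|---|---|---|
| Neither | 4.4% | 0% | 4.6% | 5.8% | 5.7% |
| Confounder 0.1 SD | 8% | 3% | 5% | 6% | 5% |
| Confounder 0.2 SD | 46% | 10% | 5.7% | 17% | 5% |
| Confounder 0.3 SD | 96% | 21% | 5% | 46% | 5% |
| Reverse path 0.2 | 93% | 23% | 93% | 5.5% | 5.7% |
| Both 0.2 | 99.9% | 34% | 93% | 16% | 4.5% |

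Covariates remove measured confounding but do nothing about direction. The lag adjusted for 12-week outcome deals with direction but still needs the covariates.

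**A lag without 12-week GPTS.** If paranoia drives reasoning, 12-week GPTS determines both 12-week fast thinking and 24-week GPTS. Under a reverse path of 0.2, three separate simulations of the lagged model without that adjustment gave 39%, 47% and 48% false positives. With it, rates were 4% to 5.5%.

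**The price of that adjustment.** Because therapy ends by about week 12, much true mediation may be complete by then, and conditioning on 12-week GPTS removes it. With genuine mediation simulated, power for the path fell from 70% to 14% under one structure and from 44% to 32% under another.

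**The instrumental variable step.** Take treatment-by-covariate as the instrument (an assumption, as none is named), with confounding and reverse paths of 0.2. An interaction of 0.2 SD on the mediator gives a median first-stage F of 4.2 and an interquartile range of the estimate from −0.34 to 0.33. At 0.3 SD these are 9.2 and −0.23 to 0.22. If the covariate also alters the direct effect on outcome by 0.1, the median estimates are 0.45 and 0.32 when the truth is zero.

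**The case against.** The strongest reply is that the protocol names the threat and answers it in stages. A reader might infer that the model adjusts only for two baseline values and excludes everything else. The text does not say so: it says the analysis will begin there, and instrumental variables follow. With valid instruments that step addresses both confounding and reverse causation. The covariate list of a secondary model is also ordinary analysis-plan content, and the SAP is not shown. This stands as a limit on the point, which concerns the stated sequence and not what the SAP may add. It does not remove it: the article chose to state its adjustment steps, and the instrumental variable check may be too imprecise at N = 300 to be the only further step.

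A reader might also infer that every planned model is concurrent. That is a fair reading of parallel growth curves, but latent change models can be lagged and the text does not say whether these are.

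It can be objected that a moderator need not be a confounder once baseline mediator and outcome are in the model. That is true, so working memory and negative symptoms are candidates and not established confounders. Their baseline timing, with that of worry and schemas, rests on Fig. 3 (not shown).

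Finally, it is tempting to make the 12-week to 24-week model the principal analysis. The working does not support that. Without 12-week GPTS it does not solve the direction problem, and with it, it answers a narrower question than mediation over 24 weeks, at lower power.

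**Conclusion.** The point holds in a limited form. The stated sequence leaves a gap for measured common causes, states no lag and does not mention reverse causation, although the article sets a causal aim and calls confounding the major challenge. The requirement for a treatment effect on both series does not close the gap, because treatment affects both in every simulated scenario.

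The size is illustrative. At an assumed 0.2 SD confounder the false-positive rate is 46% against 5.7% after adjustment; at 0.1 SD the difference is slight (8% against 5%). With confounding and a reverse path both at 0.2, the spurious proportion is about 34%, within the 30–40% range used for the power statement. The documents give none of these strengths, so a reader should not conclude that a mediation finding in this trial would be spurious. The simulations also use observed change scores in place of the latent models. With neither bias present, the stand-in keeps its 5% level (4.4%).

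**What to change.** In the mediation paragraph of Statistical analysis:

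1. Name site and the baseline values of working memory, negative symptoms, worry and schemas (where measured at baseline) beside baseline mediator and baseline outcome, in both the mediator and the outcome equations.
2. Keep the planned growth curve or latent change model as the principal analysis, and instrumental variables as a further sensitivity analysis.
3. Add a sensitivity model of 24-week GPTS on 12-week fast thinking, adjusted for 12-week GPTS and the same covariates. Report beside it the reverse model: 24-week fast thinking on 12-week GPTS, adjusted for 12-week fast thinking.
4. State that the lagged model captures only mediation arising after week 12 and has lower power, so a null result from it does not by itself refute mediation. State also that the principal model, even with covariates, does not settle direction.

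The cost is wording, a few degrees of freedom and a little extra analysis. No new data are needed. If the SAP already contains these elements, a cross-reference is enough.
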